## Abstract

**Background:**

Traditionally, system leaders, service line managers, researchers, and program evaluators hire specifically dedicated implementation staff to ensure that a healthcare quality improvement effort can “go to scale.” However, little is known about the impact of hiring dedicated staff and whether funded positions, amid a host of other delivered implementation strategies, are the main difference among sites with and without funding used to execute the program, on implementation effectiveness and cost outcomes.

**Methods/design:**

In this mixed methods program evaluation, we will determine the impact of funding staff positions to implement, sustain, and spread a program, Advance Care Planning (ACP) via Group Visits (ACP-GV), nationally across the entire United States Department of Veterans Affairs (VA) healthcare system. In ACP-GV, veterans, their families, and trained clinical staff with expertise in ACP meet in a group setting to engage in discussions about ACP and the benefits to veterans and their trusted others of having an advance directive (AD) in place. To determine the impact of the ACP-GV National Program, we will use a propensity score-matched control design to compare ACP-GV and non-ACP-GV sites on the proportion of ACP discussions in VHA facilities. To account for variation in funding status, we will document and compare funded and unfunded sites on the effectiveness of implementation strategies (individual and combinations) used by sites in the National Program on ACP discussion and AD completion rates across the VHA. In order to determine the fiscal impact of the National Program and to help inform future dissemination across VHA, we will use a budget impact analysis. Finally, we will purposively select, recruit, and interview key stakeholders, who are clinicians and clinical managers in the VHA who offer ACP discussions to veterans, to identify the characteristics of high-performing (e.g., high rates or sustainers) and innovative sites (e.g., unique local program design or implementation of ACP) to inform sustainability and further spread.

**Discussion:**

As an observational evaluation, this protocol will contribute to our understanding of implementation science and practice by examining the natural variation in implementation and spread of ACP-GV with or without funded staff positions.

Contributions to the literature
Accessing new funding is a discrete implementation strategy used to embed a new evidence-based practice into routine health care settings.Few studies in implementation science provide details on the use of financial strategies.This VA-funded partnered program evaluation will investigate how dedicated versus detailed staff impacts implementation effectiveness and cost outcomes.

## Background

Traditionally, system leaders, service line managers, researchers, and program evaluators hire specifically dedicated implementation staff to ensure that a quality improvement effort or the integration of evidence-based practices (EBPs) in healthcare settings can “go to scale.” This use of dedicated versus detailed staff to implement programs has relevance and utility within large health care organizations such as the United States (US) Department of Veterans Affairs (VA), in which the use of quality improvement exemplifies a learning health care organization. However, little is known about the impact of hiring dedicated staff and whether funded positions, amid a host of other delivered implementation strategies, are the main difference among sites with and without funding used to execute the program on implementation effectiveness and cost outcomes. Advance Care Planning via Group Visits (ACP-GV), a quality improvement project funded by VA’s Quality Enhancement Research Initiative (QUERI) and the Office of Rural Health (ORH), was developed to address this gap in the literature.

### Use of paid staff as implementation strategy

The use of paid staff to implement a program is a common practice in research and quality improvement cycles within healthcare settings. A recent unpublished systematic review of implementation financing strategies focused broadly on how implementing sites obtained funds. What is rarely reported in detail is how the implementing site spent the money. Therefore, the ability to evaluate funding positions as an implementation strategy to determine the impact on clinical, implementation effectiveness and cost outcomes is novel. Given that most grant mechanisms are predicated on the distribution of funds for the hiring of dedicated staff, the implied or implicit notion is that the funded positions will produce the desired outcomes [1].

### Developing and disseminating a scalable EBP across VA healthcare settings

In 2013, a clinical demonstration project using a novel approach to Advance Care Planning (ACP), a group visit format, was developed by [name] and colleagues in the Veterans Integrated Service Network (VISN) 16 Geriatric Research, Education, and Clinical Center (GRECC). This project, ACP-GV, has garnered acclaim first as an Office of Rural Health (ORH) Promising Practice and now as a Gold Status Practice by the VA Diffusion of Excellence Initiative (DEI). In these ACP-GVs, veterans, their families, and trained clinical staff with expertise in ACP meet in a group setting to have discussions about ACP and the benefits to veterans and their trusted others of having an advance directive (AD) in place

In fiscal year (FY) 2017, the ACP-GV Leadership Team, comprised [name] and [name], VA’s National Social Work Director, was awarded a multi-year Enterprise Wide Initiative Rural Access Solution grant from ORH. This grant funds an ACP-GV Implementation Team to deploy five implementation strategies to sites to increase ACP engagement with rural veterans. As noted in Table 1, the strategies, organized by the Expert Recommendations for Implementing Change (ERIC) [2] categorization of implementation strategies, includes the name of the implementation strategy, the activity, and the recipient. The five strategies used in ACP-GV are as follows: (1) provide seed funding for new or dedicated staff (e.g., social worker and medical support assistant) who will deliver ACP-GV in rural VHA facilities and community-based outpatient clinics (CBOCs), (2) create a learning collaborative, (3) conduct ongoing training, (4) identify and prepare champions, and (5) conduct audits and feedback against productivity benchmarks using VHA national administrative data. ORH also funds a data manager who analyzes data from ACP-GV monthly site reports and conducts a pilot cost evaluation of staff productivity.

**Table 1 Tab1:** ACP-GV National Program by ERIC clusters, strategies, activities, and recipients

ERIC strategy cluster category	Implementation strategy	ACP-GV National Program activities developed and tracked by the ACP-GV Implementation Team	Recipient
Utilize financial strategies	Access new funding	ORH funding provided for ACP-GV staff positions in rural VHA facilities and their CBOCs (e.g., social worker and medical support assistant)	Only funded sites
Train and educate stakeholders	Conduct ongoing training	Offer continuing education units to professional clinical staff for attending monthly education calls	Staff at all ACP-GV sites
Train and educate stakeholders	Create a learning collaborative	Promote use of ACP-GV Welcome, Facilitation, and Implementation Manuals on VA Pulse website to staff via weekly administrative calls	Staff at all ACP-GV sites
Use evaluative and iterative strategies	Audit and feedback	Promote use of ACP-GV Implementation Manual on process for documentation, quarterly data collection, and review performance with sites	Staff at all ACP-GV sites
Develop stakeholder interrelationships	Identify and prepare champions	Promote use of VA Pulse website to identify and to deliver materials used to inform local champions and facility leaders on program implementation and sustainability	Staff at all ACP-GV sites

The goal of the ACP-GV National Program is to reach all VA healthcare facilities (*N* = 170). However, the current ORH grant will only reach a portion (*N* = 80) of sites that are considered rural. Therefore, ACP-GV and ORH partners requested our assistance to determine the specific impact of funding staff positions amid the myriad other implementation strategies. This QUERI-funded project has as its main evaluation goal to determine the impact of funding staff positions to implement, sustain, and spread ACP-GV across the entire Veterans Health Administration (VHA).

### What is Advance Care Planning?

Traditional conceptions of ACP have been limited to establishing an advance directive (AD) document. An AD can include both a “living will,” a legal document describing preferences for treatment, and/or a Durable Power of Attorney for Health Care, also a legal document that designates a healthcare proxy to speak for them if they are unable to speak for themselves. However, completing an AD document is only a small part of a larger more complex process. Fried et al. [3] identified key behaviors that are important in advocating ACP as a process instead of an event or just a document to include when completing a living will, designating a healthcare proxy, communicating preferences or guidance, and the importance that the veteran places on quality versus quantity of life with trusted others and clinicians. The ACP-GV program noted here uses this broader conceptualization of ACP.

### Why do ACP in healthcare settings?

The lack of ACP discussions increases the risk that veterans will receive care different from what they prefer and may experience unnecessary interventions leading to increased suffering and higher health care costs [4, 5]. While VHA Handbook 1004.02 mandates personalized ACP discussions including information on AD for all patients in all VHA settings to comply with the Patient Self-Determination Act of 1990 and the Joint Commission, documentation of these discussions in VHA is challenging. This may be due to patient and provider barriers, such as a lack of veteran awareness and lack of perceived clinical priority by providers, respectively [6]. Also, in our clinical experience [7–9], ADs of VHA patients are difficult to quantify using electronic health records or administrative data retrieval systems since they are scanned or hard copy documents. Given these barriers, a new data architecture system launched in FY 20 will provide a national view of ADs across the VHA. Future studies will compare the VA to the community AD completion rate of 26% [10], yet current estimates using this community rate note that 6.7 of the 9.05 million enrolled veterans do not have an AD and may be hospitalized without their medical preferences being known.

### Challenges of Advance Care Planning

Substantial barriers exist that deter optimal ACP. Patients, their families, and healthcare providers often struggle to engage in discussions related to the topics of death and dying [11–14]. Patients often lack awareness or postpone ACP discussions until a crisis requires a life-sustaining treatment decision [15]. VHA Handbook 1004.02 designates the responsibility for ACP discussions to primary care providers. Given that the average primary care visit is about 15–30 min long, providers frequently do not have time during the visit. Although a mandated practice, it may not be perceived as a clinical priority [6]. The innovative approach of groups can also alleviate anxieties of veterans while improving both the quality [16] and efficiency of ACP. The supportive atmosphere of groups can also alleviate anxieties veterans may have when discussing this potentially complex and emotional topic individually with a healthcare provider or significant other. Furthermore, clinical staff members who lead the groups have more time to engage veterans about their preferences and can use the group dynamic to model open dialog with veterans, peers, and trusted others [17, 18].

### Aims

This program evaluation will determine the impact of funding staff positions to implement, sustain, and spread ACP-GV across the entire VHA through the following aims: (1) evaluate the impact of the ACP-GV National Program; (2) among current sites, document and compare funded and unfunded sites on the effectiveness of implementation strategies (individual and combinations) used by sites in the ACP-GV National Program; (3) determine the budget impact of the ACP-GV National Program; and (4) identify the characteristics of high-performing and innovative sites in implementing ACP. If this funding expresses greater participation in the other strategies, then there may be a mechanism of action within accessing new funding alone, or because it is in combination with the other strategies. We will explore this possibility further.

## Methods/design

### Design

This program evaluation will use mixed (e.g., qualitative and quantitative) methods [19] to determine the impact of the ACP-GV National Program. As an observational implementation evaluation (see Fig. 1), we will start by using a propensity score (PS)-matched control design and VHA administrative data to determine the proportion of ACP discussions in VHA by comparing ACP-GV sites to PS-matched control sites not implementing ACP-GV (aim 1). As a subgroup analysis, we will also determine whether individual strategies or combinations of strategies impact the outcomes of ACP discussion and AD completion rates across the VHA, with special attention to differences between current FY 2019 sites that do (*n* = 23) and do not have (*n* = 12) ORH funding (i.e., DEI-unfunded sites) (aim 2). For aim 3, we will conduct a budget impact analysis of the ACP-GV National Program. Finally, qualitative methods will be used to identify the characteristics of high-performing (e.g., high rates or sustainers) and innovative sites (e.g., unique local program design or implementation of ACP to inform sustainability and further spread) (aim 4).

**Fig. 1 Fig1:**
[figure not shown]
ACP-GV sampling plan for aims 1 and 2

### Sample

The population for this evaluation potentially includes all veterans who seek care in FY 2019 in VHA (*N* = 9.05 million). The total number of VHA facilities is approximately 170 sites. All veterans who seek VHA services are eligible to receive information on ACP and can complete an AD. Some veterans may choose to engage in an ACP discussion individually while others may elect to attend a group visit. While all veterans are eligible, not all veterans will engage in ACP discussions or ever complete an AD. Using VA administrative data, we will examine all documented ACP discussions, AD completions, and ACP-GV encounters to estimate the sample. In FY 2019, there were 23 funded sites and 12 unfunded sites (i.e., no funding for dedicated staff positions), for a grand total of *N* = 35 sites.

### Data sources

There are three main data sources for this evaluation: (1) VHA administrative data including data obtained from the VA Corporate Data Warehouse, for data at the patient, provider, clinic, and facility levels; (2) ACP-GV Implementation Team Site Tracking Reports, monthly reports from sites on mandatory data elements, Diffusion of Excellence Initiative hub site-level entries, and national data collected on the sites’ participation from initial recruitment to full participation in all of the ACP-GV National Program implementation activities noted in Table 1; and (3) ACP-GV Evaluation Team qualitative interviews, which will collect data on budget impact and implementation consequences, characteristics, and innovations.

The VHA administrative data used here obtains data from the VA Corporate Data Warehouse which includes patient (e.g., name, social security number), provider (e.g., document definition, stop codes, visit date), site (e.g., site name and number), note title (e.g., AD note, AD discussion, AD rescinded, other AD note category), and an ACP-GV-specific workload code. The ACP-GV Implementation Team Site Tracking Report was created specifically to track and to manage the ORH-funded grant activities from recruitment to full-scale implementation as an ACP-GV site. This report tracks all implementation activities offered to any VHA facility that expresses interest in and/or later applies to become a funded or unfunded site. As noted earlier, ORH funding is awarded to rural sites, typically for a social worker and medical support assistant, with the full-time employee equivalent (FTEE) level based on the site’s projected annual workload. The FTEE, amount of funding, and type of positions for staffing of each ACP-GV site is tracked by the ACP-GV Implementation Team in the Site Report.

### Data collection for aims 1 and 2

To complete aims 1 and 2, we will use VHA administrative date from the VA Corporate Data Warehouse data to create patient, clinic, facility, and site-level variables, including veteran demographics, service utilization, AD note titles, and ACP-GV workload. For aim 2, we will merge this data with site-level variables from the ACP-GV Implementation Team Site Tracking Reports, which include sites with funded FTEE and an estimate of the unfunded sites staffing patterns. We will then add to the above data collected on the ACP-GV sites’ participation in the implementation activities from the ACP-GV Implementation Team’s Site Tracking Reports.

For aim 3, we will develop protocols with the ACP-GV Implementation Team to collect new data using an adapted version of the Time Tracking Tool developed by the Behavioral Health Team Based QUERI [20], which will quantify and connect the amount of time each staff member spends in implementation activities to allow for analysis of each strategy alone or in combination. Because implementation costs will be obtained from sites at varying stages of implementation, we will define the index date of transition from pre-implementation to implementation for an individual site as the date of initial use of the ACP-GV-specific workload code and AD discussion note by that site, while sustainability will be assessed using data for the 12 months following the index date when they started implementing ACP-GV. We will reconcile this time tracking data by allocating each cost to a site-specific period (i.e., pre-implementation, implementation, or maintenance) relative to the site-specific index date to use as implementation cost data for aim 3.

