## Aim 3: Determine the budget impact of the ACP-GV National Program

### Design

To accomplish aim 3, we will follow the steps for conducting a budget impact analysis (BIA) [24] developed by the International Society for Pharmacoeconomics and Outcomes Research (ISPOR) [25] and referenced by Smith and Barnett in their discussion of the role of economics in the QUERI program [26]. Implementation- and program-level costs will be collected and analyzed to account for the full impact of the ACP-GV program at individual sites and nationally for VHA.

### Data sources for aim 3

Data will be collected for the pre-implementation and implementation periods to estimate costs associated with ACP. VHA Managerial Cost Accounting (MCA) System data will be used to estimate health care encounter and VHA payroll costs. MCA is a derived database built from standard VHA data sources that allows comparison of cost and utilization characteristics. Activities associated with implementation (implementation period only) and direct provision of the ACP-GV will be collected at the local level and aggregated for the national program. Productivity and time data will be collected using a combination of the VA Corporate Data Warehouse, the Time Tracking Tool, and stakeholder interviews conducted as part of aim 4. Costs will be assigned to these activities based on VHA payroll costs in MCA.

### Data analysis for aim 3

ACP-GV is not expected to have direct short-term impact on overall patient healthcare utilization; therefore, the focus of the analysis will be costs related to implementation and provision of ACP-GV for sites and the National Program. Changes in costs are likely to vary by site depending on the extent to which existing resources are leveraged for provision of ACP-GV. The ability to provide ACP discussions to multiple veterans in a single session via ACP-GV will offset these increased costs; however, the extent to which these two factors exist will vary by site. To estimate direct costs, the time associated with all implementation and program activities will be multiplied by the salary and fringe rate of the team member performing the activity. Each activity will be assigned to a specific time, site, and team member to allow for estimation of costs at the individual site level. Indirect implementation costs (e.g., educational materials) will be tracked and allocated to sites by the ACP-GV Implementation Team.

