To examine the budget impact at existing sites, we will compare the costs associated with ACP during the year before and after the site joined the ACP-GV National Program. Cost differences will be analyzed from the payer perspective [24]. For the national program, including all ACP-GV program costs and costs attributed to the implementation strategies identified in Table 1, VHA will be the payer. For program and implementation costs specific to a VAMC, the VA Medical Center (VAMC) budget administrator will be considered the payer. Observable characteristics that are predicted to influence the ACP budget of an individual site will be collected (e.g., VAMC size). Using TreeAge software, a probabilistic sensitivity analysis (PSA) will be conducted [27]. The PSA allows the assignment of a distribution to model parameters rather than just a point estimate to account for uncertainty in the BIA model. To facilitate broader implementation of ACP-GV, a decision analysis model is needed for non-participating sites to estimate the budget impact at their site based on site-specific factors (e.g., VAMC size). The model will be developed in Microsoft Excel, and a user guide will be created and disseminated to sites. This model will show the budget impact at existing ACP-GV sites as well. One-way sensitivity analyses will be possible within the model to allow decision-makers to see the impact of each site-specific factor.

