## Aim 4: Identify the characteristics of high-performing (e.g., high rates or sustainers) and innovative sites (e.g., unique local program design or implementation of ACP) to inform sustainability and further spread

### Sampling plan

We will purposively select approximately 24 ACP sites. We will use site reports and our aims 1 and 2 VA Corporate Data Warehouse datasets to identify a total of six sites with high-performing characteristics (i.e., three sites with high productivity in terms of ACP-GV against the performance goal of 200 ACP-GV groups a year/per FTEE and three sites with high rates of AD discussions in the 75th or higher percentile nationally) and six sites that are sustainers after the intensity of implementation strategies begins to reduce (i.e., three sites that meet the ACP-GV performance goal and three sites with high rates of AD discussions). To capture unique site-specific program design or other innovations that might be missed by identifying sites based only on performance, we will identify six sites based on unique local program design characteristics and six with innovative models for implementing ACP known to the ACP-GV Leadership or Implementation Team or from data in the ACP-GV Implementation Team Site Tracking Report.

### Data collection for aim 4

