### Trial status

The Institutional Review Board at Central Arkansas Veterans Healthcare System has approved this program evaluation. Data collection for this program evaluation began in October 2019.

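### Sustainability is assessed from the first day of implementation, and Aim 3 has two time anchors and conflicting cost periods

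*Protocol article*

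**What the plan says.** The Aim 3 paragraph under Data collection for aims 1 and 2 sets a site-specific clock, which starts when a site first records the program's own code together with a note of an advance directive discussion: "we will define the index date of transition from pre-implementation to implementation for an individual site as the date of initial use of the ACP-GV-specific" (the sentence then names these two records). Later in the same sentence comes the sustainability rule: "while sustainability will be assessed using data for the 12 months following the index date when they started implementing ACP-GV". Time-tracking data are then reconciled by "allocating each cost to a site-specific period (i.e., pre-implementation, implementation, or maintenance) relative to the site-specific index date".

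Data sources for aim 3 names two of those three periods: "Data will be collected for the pre-implementation and implementation periods to estimate costs associated with ACP". It adds: "Activities associated with implementation (implementation period only) and direct provision of the ACP-GV will be collected at the local level".

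Data analysis for aim 3 sets the budget comparison at existing sites on another date: "we will compare the costs associated with ACP during the year before and after the site joined the ACP-GV National Program".

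The Aim 4 sampling plan gives sustainment a different meaning. It will select "six sites that are sustainers after the intensity of implementation strategies begins to reduce".

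The Aims make sustaining the program part of the evaluation's purpose. The Discussion says the results should help partners plan for the time when money for extra posts has ended.

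**The concern.** Sustainment is what remains after the launch effort has eased. A window that opens when implementation begins measures, at least in part, uptake under active support. A site could look well sustained on that window while its funding and coaching were still in place. The result would not answer the question in the Discussion, and it would not match the group of sites that Aim 4 interviews as sustainers.

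For costs, the budget impact depends on where the before and after years are cut and on whether activity before the first coded visit is counted. A non-participating site that uses the planned spreadsheet model needs the start-up cost. If the sections are applied differently, that cost may be dropped or placed in the wrong period.

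**Working it through.** The plan states no figure on this point, so there is none to reproduce. The check is interval arithmetic on the stated windows plus a comparison of the sections.

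**1. Sustainability window against implementation**

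Inputs: index date = month 0 and sustainability window = months 0 to 12, both from Data collection for aims 1 and 2. Implementation runs from month 0 to month M. M is not given, so it is assumed over a range.

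Share of the window inside implementation = min(M, 12) / 12.

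| Assumed M (months) | Share |
|---|---|
| 3 | 3/12 = 25% |
| 6 | 6/12 = 50% |
| 9 | 9/12 = 75% |
| 12 or more | 12/12 = 100% |

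The share is above zero for every M above zero. Some overlap follows from the text alone; its size does not.

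**2. Number of cut points**

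Three consecutive periods need two boundaries. The article gives one, the index date, which separates pre-implementation from implementation. The start of maintenance is undefined, so costs after the index date cannot be divided between the last two periods.

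**3. Two anchors**

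Inputs: cost periods are cut at first code use (Data collection for aims 1 and 2), and the budget comparison is cut at joining (Data analysis for aim 3). Let a site join L months before its index date. L is not given, so it is assumed.

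Share of the year after joining that precedes the index date = L / 12, for L up to 12.

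| Assumed L (months) | Share |
|---|---|
| 0 | 0% |
| 1 | 1/12 = 8% |
| 3 | 3/12 = 25% |
| 6 | 6/12 = 50% |
| 12 | 12/12 = 100% |

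The two anchors agree only if L = 0. For any other lag, the same months are pre-implementation on one clock and part of the after year on the other.

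**4. Which activity is costed**

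- Data collection for aims 1 and 2: each cost goes to pre-implementation, implementation or maintenance.
- Data sources for aim 3: data cover pre-implementation and implementation, maintenance is not mentioned, and implementation activity is limited to the implementation period.
- Data sources (the general section): the Site Tracking Report follows activity from recruitment onward, so activity can precede first code use.
- Data analysis for aim 3: the time for all implementation and program activities is costed, and national costs include those of the Table 1 strategies.

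If the index date governs, the restriction in Data sources for aim 3 would leave uncollected the activity between joining and first code use. The other three statements point to counting it. They cannot all be followed as written.

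**The case against.** The strongest reply is that several larger conclusions do not follow, and that is right.

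- A reader might infer that the 12 months are the implementation period itself, an overlap of 12 out of 12. No section says how long implementation lasts, and maintenance is listed as a separate period, so part of the window could be maintenance.
- A reader might infer that start-up costs are omitted altogether. The article also commits to costing all activities and to tracking from recruitment. Pre-implementation in Data sources for aim 3 could also mean the comparator year before joining, when little program activity would be expected. Start-up work would then fall in the after year and be counted. This is a contradiction to reconcile, not a proven loss.
- A reader might infer biased costing because the Time Tracking Tool supplies new data and "Data collection for this program evaluation began in October 2019", after the existing sites had joined. But Data sources for aim 3 names Managerial Cost Accounting data, the warehouse and interviews as well, so no bias is shown.
- A year counted from joining is a legitimate budget view, since the payer bears ramp-up costs. The lag percentages illustrate how far the clocks can differ; they do not measure error.
- Sustainability is mainly examined in Aim 4, not all sites have funded posts (12 of 35 do not), and the Aim 1 primary outcome is unaffected.

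It may also be said that a condensed article leaves exact boundaries to later protocols. That could excuse an unstated boundary. It does not excuse a window that the article states and that starts on the wrong side of any such boundary, nor stated rules that disagree.

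**Conclusion.** The sustainability rule is wrong as written. Its window starts with implementation, conflicts with Aim 4's meaning of a sustainer, and cannot inform sustainment once funding and strategies taper. This rests on the article's wording alone. The extent of overlap depends on an implementation length the article does not give: 25% to 100% for assumed lengths from 3 months to 12 or more.

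Aim 3's two anchors, the missing start of maintenance and the conflicting collection periods also stand as contradictions. Their consequence is a risk that start-up costs are left out or misallocated. The size of any budget error cannot be derived, because neither the lag from joining to first code use nor the costs in it are stated.

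**What to change.** - State when implementation ends: for example month 12 after the index date, or the recorded date on which strategy intensity falls, as in Aim 4. Assess sustainability only after that point.
- Use one time scale in Data collection for aims 1 and 2, in the Aim 3 data-source and analysis sections, and in the Aim 4 sampling plan. Define both the joining date and the index date on it, call joining to index date pre-implementation, keep that distinct from the comparator year before joining, and say which date the after year is counted from.
- In Data sources for aim 3, collect implementation activity in both the pre-implementation and implementation periods, and say whether maintenance costs are collected.
- Report start-up cost, from joining to index date, as its own line in the budget impact results.

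The cost is mainly revised wording and re-cutting of data already planned for collection. The real downside is that recently started sites contribute no sustainability data until they pass the stated end of implementation.
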